The iSeFallED study aims to address these challenges by implementing tailored and scalable secondary prevention into clinical practice. Furthermore, it will evaluate the feasibility and acceptability of a rapid risk assessment tool in the ED, followed by a comprehensive geriatric assessment in a specialized falls clinic and a six-month intervention period. It will also assess the efficacy with respect to maintaining independence in the activities of daily living post-fall, while exploring the effects of different exercise interventions on secondary outcomes such as quality of life and falls incidence. In addition, the iSeFallED study will investigate the feasibility of treadmill perturbation-based balance training in a clinically diverse and heterogenous population. By integrating sensor-derived data with machine learning methods for the detection of gait disturbances, and by examining individual barriers, preferences, and needs, iSeFallED aims to optimize the implementation process and evaluate the feasibility of initiating secondary falls prevention in the ED setting.

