### Implementation process

The iSeFallED study utilizes the RE-AIM framework (Reach, Efficacy, Adoption, Implementation, Maintenance), which was designed to evaluate interventions to improve general health, to guide and assess the implementation process [24]. The RE-AIM framework has been previously analyzed in a systematic review on physical activity-based falls prevention [25], concluding that all five key domains should be reported. In the iSeFallED study, these domains will be addressed as follows: *(1) Reach* – The study will assess the number and characteristics of patients identified as high risk in the ED and the proportion referred to the geriatric university outpatient clinic. Representativeness will be evaluated by comparing participant demographics with those of the broader ED population experiencing falls, the historical control group, and total admissions at the recruiting centers. *(2) Efficacy* – The efficacy of the intervention will be measured by evaluating functional outcomes, maintenance of daily activities, and secondary outcomes such as quality of life and fall recurrence. Additionally, unintended positive or negative effects will be documented. The outcomes will be compared with the historical study population of the SeFallED study, which underwent similar measurements. *(3) Adoption* – The study will analyze the extent to which healthcare professionals integrate the risk assessment tool and referral pathway into their workflow. Adoption at the institutional level will also be assessed, identifying facilitators and barriers to uptake. *(4) Implementation* – Regarding this dimension, adherence to the intervention will be evaluated at both provider and patient levels. It will assess the consistency of administering risk assessments and referrals in the ED, as well as patient participation in geriatric university outpatient clinic interventions, including adherence to prescribed exercise programs. Time and resource constraints affecting implementation will also be considered. *(5) Maintenance* – The study will examine the sustainability of integrating falls risk assessments and referrals into routine ED practice, as well as the long-term impact on patients, including continued engagement in falls prevention activities six months post-intervention. By systematically evaluating these dimensions, the iSeFallED study aims to provide a comprehensive understanding of the feasibility, effectiveness, and sustainability of embedding secondary falls prevention into ED care. In addition, the study will draw on key principles and guidance from the framework for developing and evaluating complex interventions to ensure a theoretically grounded and context-sensitive approach. This will support the translation of findings into practical strategies for broader implementation across diverse emergency care settings [26].

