### Data assessment

Data will be collected at the ED, in participants’ homes, in the geriatric university outpatient clinic and at the gait laboratory. Furthermore, Inertial Measurement Units (IMUs) to measure physical activity as well as gait parameters will be worn by the participants during daily life over seven days at each time point (T1 – T3). After the initial assessment, the researchers maintain contact with the participants through monthly phone calls, as part of the prospective falls recording in addition to fall calendars (Fig. 1). First data assessment will be within four weeks of presenting to the ED. Whereas participants in Arm 1 will be visited at home for the first functional assessment (T1), participants in Arms 2 and 3 will be assessed in the geriatric university outpatient clinic and additionally via telephone interview. Data collection after the intervention (T2) and twelve months after presenting to the ED (T3) will be scheduled at participants’ homes.

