### Statistical analysis and sample size calculations

Descriptive analyses will summarize participant characteristics, including age, sex, place of residence, level of education, and intervention choice. Differences between groups in these characteristics, as well as adherence to the assigned or selected interventions and the proportion of participants who attend the health sport activities, will be explored to assess feasibility and representativeness.

Feasibility of the training interventions will be assessed by documenting AEs and SAEs, as well as dropout rates, while acceptability will be evaluated through focus groups. The effectiveness of the tailored interventions in the iSeFallED study will be analyzed using a Wilcoxon-Mann-Whitney test, comparing endpoints between the historical control group (SeFallED) and the new study population. The primary outcome will be the change in Activities of Daily Living (ADL) scores between T2 (6 months) and T3 (12 months) using ADL scores from Jonkman and colleagues [39].

An independent statistician performed the sample size calculation to assess effectiveness. This calculation was based on data from 257 participants in the previous SeFallED project, who were followed over a 12-month period. For the iSeFallED study, it was assumed that the tailored interventions would result in a clinically meaningful improvement of at least 1 point in ADL score in individuals with at least a moderate risk of functional decline [39]. No difference is expected for individuals in Arm 1 (mild risk) compared to the historical control group. Data from the previous study indicated that approximately one-third of participants exhibited a low risk of functional decline (Arm 1), while two-thirds had at least a moderate risk (Arms 2 and 3). Consequently, an expected difference (Δ) of 0.67 points in the ADL score was determined for the new study (iSeFallED).

To detect a meaningful difference in ADL scores between T2 and T3 with a power of 90% at a significance level of α = 0.05, a total of 246 participants is required. Accounting for an estimated dropout rate of approximately 20% (based on a 17% dropout rate in the previous study), the necessary sample size increases to 308 participants. To further strengthen the study’s robustness and allow for secondary, exploratory analyses, a total sample size of 350 participants is planned.

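### The primary outcome is ADL change from T2 to T3, a window that opens after the six-month intervention and so largely leaves out the period in which the programme is delivered

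*Protocol article*

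**What the plan says.** The primary outcome is defined under Statistical analysis and sample size calculations in the Protocol article: "The primary outcome will be the change in Activities of Daily Living (ADL) scores between T2 (6 months) and T3 (12 months", using the Jonkman ADL score. The sample-size paragraph of that section uses the same window: "To detect a meaningful difference in ADL scores between T2 and T3 with a power of 90% at a significance level of α = 0.05". It assumes that the tailored interventions improve ADL by at least 1 point in the participants at moderate or higher risk (two-thirds of the sample) and by nothing in the rest. This gives an expected difference of 0.67.

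The timing is set elsewhere:
- **T1.** Data assessment says "First data assessment will be within four weeks of presenting to the ED".
- **Intervention.** The aims at the end of Background describe ED screening "followed by a comprehensive geriatric assessment in a specialized falls clinic and a six-month intervention period".
- **T2 and T3.** Data assessment has "Data collection after the intervention (T2) and twelve months after presenting to the ED (T3".

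Two further places bear on purpose. The aims say of the study: "It will also assess the efficacy with respect to maintaining independence in the activities of daily living post-fall". Implementation process lists Efficacy and Maintenance as separate domains, and Maintenance includes "continued engagement in falls prevention activities six months post-intervention". Table 2, row 6, schedules the Jonkman index at T1, T2 and T3.

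**The concern.** A change score that starts at T2 uses a post-treatment baseline. Most of what the Intervention section describes is delivered before that point: the medication review at the first clinic visit, the home-programme support visits in weeks three and six, the six-month sports-club reimbursement, and the optional treadmill sessions within three months of inclusion. Any ADL gain from these that is present at T2 is removed from the primary outcome.

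The sample size nevertheless places the whole gain between T2 and T3, and the protocol gives no reason why it should arise there. A T2-T3 comparison also cannot tell a programme that did nothing from one whose gain was fully kept, because both have an expected difference of zero. What is at stake is that a programme that helped could be reported as ineffective, or as harmful, on its primary outcome.

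**Working it through.** **1. The plan's own figures**

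- Diluted effect: 2/3 × 1 + 1/3 × 0 = 0.67. This agrees with the plan.
- Dropout: 246 / (1 - 0.20) = 307.5, so 308. This agrees with the plan.
- The 246 cannot be reproduced, because no SD is given. It can only be solved backwards. With two-sided α = 0.05 (sidedness is not stated, so this is an assumption) and 90% power, the required standard error is 0.67 / (1.960 + 1.282) = 0.2067. The implied SD is 0.2067 / √(1/n₁ + 1/n₂):
  - 246 as both groups together (123 and 123): SD 1.62
  - 246 in each group: SD 2.29
  - 246 new participants against 257 historical controls: SD 2.32

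A Wilcoxon efficiency of 0.955 lowers these slightly, to 1.58, 2.24 and 2.26. I use 1.62, 2.32 and 3.0 as the range. The top value is an assumption, added to show a less favourable case.

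**2. What the T2-T3 window measures**

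Let the between-group benefit be 0.67 at T2 and r × 0.67 at T3, where r is the share kept. Positive means better function in iSeFallED.

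- T2-T3 contrast = (r - 1) × 0.67
- T1-T3 contrast = r × 0.67

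That the benefit is in place by T2 is an assumption; the plan does not say when it accrues.

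| Share kept, r | T2-T3 difference | T1-T3 difference |
|---|---|---|
| 2 | +0.67 | +1.34 |
| 1.5 | +0.335 | +1.005 |
| 1 | 0 | +0.67 |
| 0.75 | -0.1675 | +0.5025 |
| 0.5 | -0.335 | +0.335 |
| 0 | -0.67 | 0 |

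The signs do not depend on the SD. The planned +0.67 on T2-T3 appears only at r = 2, when the benefit doubles after T2.

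**3. Chance of a misleading result**

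Analysed numbers: 350 × 0.80 = 280 new participants against 257 controls. The protocol does not state the number of controls in the comparison, so 257 is an assumption. SE = SD × √(1/280 + 1/257). By normal approximation to the two-group comparison:

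- P(significant and favourable) = Φ(difference/SE - 1.96)
- P(significant and unfavourable) = Φ(-difference/SE - 1.96)

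Example: with SD 2.32, SE = 0.200. At r = 0.5, Φ(0.335/0.200 - 1.96) = 0.39.

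| T2-T3 result | SD 1.62 | SD 2.32 | SD 3.0 |
|---|---|---|---|
| r = 1, significant benefit | 2.5% | 2.5% | 2.5% |
| r = 0.75, significant apparent harm | 22% | 13% | 9% |
| r = 0.5, significant apparent harm | 67% | 39% | 25% |

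The 2.5% at r = 1 is simply the upper-tail type I error when the true difference is zero.

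**4. The same benefit measured from T1**

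If the T1-T3 change had the same SD (an assumption, to be replaced by SeFallED data), power at r = 1 would be Φ(0.67/SE - 1.96): 99.8%, 92% and 73% for SD 1.62, 2.32 and 3.0.

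**The case against.** - **The effect may build after T2.** This is the strongest point. A reader might infer that the endpoint must give a null or reversed result for any effective programme. The documents do not support that. They do not say when the 1-point gain accrues, participants may go on exercising, and controls may decline later. In those cases the T2-T3 difference could be positive. This makes the conclusion conditional but does not rescue the endpoint: the planned 0.67 would need the benefit to double after T2, nothing in the protocol argues for that, and a T1-T3 window would capture late divergence too.
- **The intervention period may not be wholly excluded.** T1 can fall up to four weeks after the ED visit. If the six-month label on T2 counts from that visit, the last weeks of the programme could lie after T2. This stands, but the overlap is small, so the window largely rather than entirely leaves the intervention out.
- **It may be a reporting slip for a window starting at T1.** A reader might take the two mentions as proof of a deliberate choice. Both stand in one section and the second may repeat an error in the first; the abstract names no window. The documents do not settle it. Either way, the text needs correction.
- **Maintenance is a legitimate question.** It is, but the protocol itself separates it from efficacy.
- **T1 has weaknesses of its own.** Arm 1 is assessed at home, Arms 2 and 3 in the clinic and by telephone, and the protocol says only that the controls had similar measurements. This stands and belongs in the fix.

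**Conclusion.** The concern holds in conditional form. As written, the primary outcome and the power statement rest on a window that begins after the intervention. That window does not match the efficacy aim, and its expected difference is zero or negative if the benefit is gained by T2 and then kept or partly lost. Fully kept, the chance of a significant favourable result is about 2.5%, not 90%. At 75% and 50% kept, the expected differences are about -0.17 and -0.34, and the chance of significant apparent harm is about 22% to 9% and 67% to 25% over SD 1.62 to 3.0.

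The direction rests only on the benefit accruing by T2. The percentages also rest on an SD the protocol does not state, on 280 against 257 analysed, and on a normal approximation; they are illustrations. Because the problem sits in the primary outcome, it must be resolved before outcomes are analysed.

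**What to change.** 1. By a dated, justified amendment before outcome analysis, define the primary outcome with T1 as baseline and one named end point. T3 fits the 12-month follow-up; T2 is also defensible. The choice should be stated once and used in both the outcome definition and the power statement.
2. Keep T2-T3 as a secondary maintenance outcome.
3. From the SeFallED data, estimate the SD for the chosen window, state it, and restate the power for the planned 350.
4. Confirm that SeFallED holds a comparable T1 Jonkman score, and say how the difference in T1 setting between arms will be handled.

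**Cost.** The T1 Jonkman score is already scheduled in Table 2, so iSeFallED needs no new data collection. The price is an amendment to the primary outcome in a study whose stated period began in October 2024, one rerun of the sample-size calculation, and a restated power that may be less favourable than 90%. The registry entry is not among the documents, so whether it also needs changing should be checked.

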### Data management

Data will be managed using unique and pseudonymized study codes. These will be used to code and file all electronic information that will be stored on secured university systems. Paper and pencil tests will be stored in a cabinet with a lock. Data will be integrated into a custom-made Research Electronic Data Capture (REDCap) database hosted at the Carl von Ossietzky University Oldenburg. Data will be collected via REDCap Mobile App using a tablet owned by the university. REDCap is a secure, web-based software platform, designed to support data capture for research studies [69, 70].

### Patient and public involvement

A participatory research team (PRT), which was approved by the Medical Ethics Committee of the University of Oldenburg (number 2024–160), will be involved as consultants. The PRT consists of older adults, who have themselves experienced a fall before, and individuals from the health sector, such as exercise group instructors or counseling centers for individuals with cognitive impairment. Four members of the PRT already took part in the previous study and provided feedback to study planning. Approximately 26 meetings between researchers and the PRT will take place throughout the course of the iSeFallED study. The PRT will provide feedback for example to the comprehensibility of consent forms, the burden of the assessment batteries, strategies of participant recruitment and the guidelines for the focus group interviews. All meetings between the PRT and the researchers will be documented with focus on the remarks of the PRT. The PRT’s feedback, and whether and to what extent it will lead to changes in study procedures, will be documented. Furthermore, semi-structured telephone interviews will be performed with all members of the PRT to evaluate their integration and participation in the research process. An independent researcher, not participating in meetings with the PRT, will conduct the interviews. Audio data from interviews will be transcribed with two multidisciplinary independent researchers analyzing the data. Content analysis according to Kuckartz [61] will be applied with deductively derived categories from previous studies about PRTs and inductively derived categories from the recorded material [64]. Members of the PRT will receive an expense allowance of 25€ per hour according to documented working hours, which include meetings and working tasks between meetings.

## Discussion

Falls represent a major public health challenge, particularly in the context of an ageing population. Although effective strategies for both primary and secondary falls prevention exist, their implementation remains difficult. This is especially evident in clinical settings, where barriers such as limited financial and personnel resources, as well as the heterogeneity of patient populations, hinder the delivery of evidence-based interventions. The iSeFallED study aims to address these challenges by evaluating the implementation of a tailored secondary falls prevention program for older individuals presenting to the ED following a fall.

The present study employs a risk stratification scheme specifically adapted for the ED context, using data from a previous observational study that followed a comparable study population using similar inclusion and exclusion criteria [22]. Implementing risk stratification is essential for delivering tailored interventions – both to optimize healthcare resource allocation and to meet individual functional as well as personal abilities. The importance of fast fall risk identification has been emphasized by global guidelines for falls prevention, which introduced a risk stratification scheme for older adults [5]. While this may represent an important milestone in patient care, such schemes have been critically discussed as they often lack adaptability to local contexts and resources [71]. Moreover, their applicability to specific patient cohorts may be challenging, prompting several refinements of the original framework to improve predictive accuracy [72, 73]. In the original guideline-based scheme, all individuals presenting to emergency services after a fall are classified as having experienced a severe fall, thereby being deemed at high risk for future falls and functional decline. However, data from the observational study SeFallED suggests that this is not always the case – particularly for individuals discharged directly from the ED without further inpatient care [74]. For this subgroup, a distinct risk stratification approach may provide greater accuracy and contextual fit. Therefore, the iSeFallED study will assess whether ED-specific risk stratification derived from the SeFallED data is both feasible and accurate, and whether it is acceptable to participants.

To evaluate feasibility, efficacy, and implementation procedure, iSeFallED adopts a pragmatic mixed methods trial design. Quantitative measures – including activities of daily living, monthly fall incidence (via telephone follow-up), adverse events, and dropout rates – will assess feasibility and efficacy. Acceptance within the target population will be assessed qualitatively through focus groups similar with previous approaches [75–78]. Integrating multiple data sources is essential to advance understanding of secondary falls prevention strategies. To ensure alignment with priorities of the patients and healthcare providers, a PRT – including stakeholders, patient representatives, and health service providers – will support the study. Early involvement of these groups can enhance the relevance, design, and acceptability of interventions. In health services research, such participatory approaches are increasingly recognized for improving recruitment, fostering relevance, and enhancing research quality [79, 80].

A further strength of the iSeFallED study lies in the diversity of its intervention delivery. While the falls prevention interventions focus on strength and balance training – reflecting the strongest evidence identified in the global guidelines for falls prevention [5] – its delivery is tailored to individual needs and preferences, offering both home-based and group-based solutions either at the university center or in local sports clubs. For participants at mild risk, iSeFallED offers education and advise on falls prevention and physical activity, which is recommended by the global guidelines for falls prevention [5]. Furthermore, to include an innovative approach, the study offers treadmill perturbation-based balance training to all participants. This task-specific training of dynamic balance response has shown promising effectiveness in previous studies [6, 7], and its feasibility in an unselected, heterogenous clinical population will be evaluated.

Incorporating treadmill-based perturbations also enables further refinement of the previously developed machine learning algorithms [65, 67]. Automated detection of gait disturbances could improve early identification of individuals at risk for recurrent falls and enable more targeted intervention prescriptions. This approach aligns with a recent call to action from the European Geriatric Medicine Society Special Interest Group on Falls and Fractures, which emphasizes both the translation of evidence-based recommendations into real world settings and the advancement of technology-assisted systems [81]. By evaluating data from wearable devices such as smartphones, smartwatches, and hearables, the study will provide novel insights into detecting gait disturbances in daily life, using routinely worn monitors.

Successful recruitment and sustained adherence are key factors to the success of the study, with participant drop-out during the 12-month follow-up presenting a substantial risk. To address this, a well-established and previously evaluated recruitment process will be implemented, with research personnel present in the ED Monday through Friday to engage directly with potential participants [12]. In addition, nurses and physicians in the ED will receive training to distribute study information flyers to patients who meet the inclusion and exclusion criteria outside of working hours of the research team. A centralized point of contact for individuals at risk – via a geriatric university outpatient clinic – will be provided, in accordance with prior research recommendations [17]. By offering tailored interventions, the study aims to optimize the “burden to benefit ratio” for participants, which may improve recruitment and retention compared with the previous observational study (SeFallED). Secondary analyses will assess whether the different intervention deliveries yield comparable benefits. As standardization is more challenging in home-based programs and community sport club settings than in the laboratory setting of an intervention undertaken by the study staff itself, iSeFallED will provide important insights into the relative effectiveness of varied delivery approaches.

The iSeFallED study will employ the study participant cohort from the prior SeFallED study as a historical control group [82], thereby addressing the well-recognized recruitment challenges associated with vulnerable patient populations. This design allows the study to better reflect real-world clinical practice, as RCTs frequently exclude a substantial proportion of patients, and, thus, limit generalizability. By maintaining inclusion and exclusion criteria consistent with those used in the previous study, iSeFallED seeks to extend understanding of the clinical effectiveness of secondary falls prevention within routine healthcare contexts [27, 83]. While this approach increases the effective sample size and enhances external validity, several limitations must be acknowledged. Participants enrolled during the earlier study may have been subject to different global or local circumstances, which could influence outcome trajectories. To mitigate potential biases inherent to the use of historical controls [82, 84], the baseline characteristics between the two study populations will be systematically compared, and statistical models will be adjusted for any identified differences by the study biostatistician.

The findings of iSeFallED will inform the feasibility, acceptability, and effectiveness of a secondary prevention program for older individuals presenting to the ED after a fall but not requiring hospitalization. The study will also evaluate implementation success within the complex and resource-limited ED environment, offering opportunities to refine processes to improve outreach and inclusivity in healthcare services for older adults. Furthermore, it will refine automated gait disturbance detection using machine learning algorithms and assess its feasibility in real-life data. Through its mixed-methods design, iSeFallED has the potential to serve as a model for integrating secondary falls prevention interventions into clinical practice, ensuring accessibility and scalability for a broader population.

